## Ethics and dissemination

### Ethical approval, regulation and governance

The investigators will conduct the study in accordance with relevant regulations and with the Declaration of Helsinki, complying with the Good Clinical Practice ICH E6(R2) and latest versions, where applicable.

Ethical approval was obtained from the Berkshire Research Ethics Committee (REC) (Reference: 24/SC/0309). Health Research Authority and Health and Care Research Wales approved the study. MHRA, which regulates the use of the unlicensed vaccine and the comparator in the study, has authorised the trial. It is registered with ISRCTN under ISRCTN65855590.

Annual reports will be prepared, including a development safety update report.

### Safety and potential risks

There are several potential risks associated with the trial conduct, such as study fatigue, phlebotomy-related complications, vaccine-related adverse events and challenge-associated risks. The study is covered by a clinical trials insurance policy.

Serious adverse events (SAEs), as defined in the online supplemental table S9, will be monitored from the time of enrolment. Any vaccine-related SAE will also be reported as SUSAR (suspected unexpected serious adverse reaction) to all principal investigators, sponsor-delegated investigators, MHRA, REC and other relevant authorities, according to regulations.

If group holding rules, shown in the online supplemental figure S2, are triggered, the study will be paused pending a review by the sponsor and the DSMC, and MHRA and REC will be notified. The decision to terminate the trial or to proceed will be based on the available evidence on the safety of the vaccine. When deemed safe to proceed, a request to the MHRA and Ethics Committee will be submitted, which may include an amendment with changes to the protocol, to the Participant Information Sheet and to the reference safety information of the vaccine Investigator Brochure, as applicable.

The DSMC comprises five independent experienced researchers who will provide real-time safety oversight.

Study fatigue and mood disturbances will be monitored throughout the study with the application of Hospital Anxiety and Depression score questionnaire^57^ at screening, prevaccination and prechallenge visits; additionally, there will be a daily mood question in the challenge diary. Phlebotomy-related complications are rare; they will be monitored clinically and by laboratory results and managed by the study clinicians. Should a participant develop anaemia during this study, sample volumes will be minimised to include only essential safety blood tests, including blood cultures, where appropriate.

Individual participants will be discontinued from the trial in case of a critical protocol deviation, vomiting within 90 min from challenge administration or severe adverse reaction to the vaccine. At least the safety follow-up will be completed until day 180, provided participant consents to it.

#### Vaccine candidate SII-TCV(B)

A phase I controlled randomised study conducted in 60 healthy adults in India demonstrated the safety of the vaccine, with no SAEs and no long-term potential risks to recipients.^18^ Most commonly reported symptoms (injection site pain, headache and myalgia) were all of mild to moderate severity.^18^ To reduce the risk of hypersensitivity, volunteers with a history of allergy or intolerance to any of the vaccine components will be excluded.

Participants will be provided details for contact with a study doctor 24 hours a day, 7 days a week. Additionally, study teams will have participants’ contact details and also details of a 24-hour contact nominated by the participants.

#### Comparator vaccine Typhim Vi

Local reactions such as pain, swelling and redness at the injection site are the most common adverse reactions following this vaccine and are usually mild and transient, based on estimates from clinical trials and postmarketing surveillance data.^49 58^ Rare cases of anaphylaxis after its administration were reported.

#### Challenge

Some participants may develop symptoms of paratyphoid fever during the challenge phase, and there is a potential risk of severe disease. To mitigate risks, common symptoms of enteric fever and its severity will be monitored closely during the challenge phase during visits and via an electronic diary (online supplemental table S5), and severe disease, as defined by prespecified criteria (see box 2), will be monitored. Additional to an in-clinic daily review, the study doctor will review blood results and e-diary entries every evening. Antibiotics will be initiated within 24 hours (typically much sooner) of diagnosis criteria being met or on day 14 postchallenge, whichever occurs first. Due to a mild-moderate symptom profile,^43 48 59^ most participants are expected to be diagnosed with the endpoint of positive blood cultures rather than as a result of persistent fever.

Box 2Adverse events for special consideration related to challenge and criteria for severe paratyphoid A diseaseAdverse events for special consideration related to challengeSevere paratyphoid A infection, as defined in the protocol:Oral temperature >40.0ºC.Systolic blood pressure <85 mm Hg.Significant lethargy or confusion.Gastrointestinal bleeding.Gastrointestinal perforation.Any grade 4 laboratory abnormality.Failure to clinically or bacteriologically cure a participant of paratyphoid A infection: defined as persistent clinical symptoms or persistent bacteraemia within 14 days of start of effective antimicrobial treatment.Progression to convalescent shedding of bacteria: defined as positive stool culture at least one week after completion of second course of antibiotics, in line with United Kingdom Health Security Agency (UKHSA) guidance.Progression to chronic carrier state: defined as positive stool culture at least one year following challenge.Relapse of paratyphoid A infection: defined as recurrence of confirmed paratyphoid A infection following successful treatment.Transmission of S. Paratyphi A to a contact of a participant.Adverse events requiring a physician visit or emergency department visit which, in the opinion of study staff, are related to the challenge with S. Paratyphi A.

Participants will be informed of the possibility of complications of S. Paratyphi A infection during screening, such as intestinal perforation or haemorrhage. However, this risk is low, as such complications occur almost exclusively in patients who do not receive appropriate treatment for over 2 weeks.^60^

There is a small risk of relapse of infection, defined as recurrence of confirmed paratyphoid infection following successful treatment, typically within 4 weeks of treatment. Participants will be informed of this and advised to contact the study doctor if symptoms recur. Relapse will be managed with a repeat course of antibiotics.

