**Trial registration number:**

ISRCTN65855590.

STRENGTHS AND LIMITATIONS OF THIS STUDYThe multicentre, randomised, double-blind, controlled design of the study, with stratified allocation, will provide high-quality data.The use of a controlled human infection model will enable efficacy assessment of the first bivalent typhoid-paratyphoid A vaccine candidate, since field trials are not considered feasible due to the high cost and large sample size required.Rigorous screening procedures, including gallbladder ultrasound, prevention of chronic faecal carriage of *Salmonella* enterica Paratyphi A and enforced infection control precautions, ensure safety of the participants and their close contacts.A centralised administration of challenge associated with fully validated centralised immunogenicity assays (including anti-Vi and anti-LPS IgG and IgA for primary and secondary objectives) will provide consistent endpoints.The sample size was calculated to provide 90% power to detect a vaccine efficacy higher than 30% and to demonstrate non-inferiority of Serum Institute of India–Typhoid Conjugate Vaccine(B) compared with a plain polysaccharide typhoid vaccine as control.

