#### Follow-up visits

After the challenge phase, follow-up visits occur at days 28, 90 and 180 for safety monitoring and for sampling.

To confirm SPA clearance, all participants will bring three faecal samples at least 48 hours apart, at least 1 week after completing antibiotics. When all three samples are culture-negative for SPA, faecal clearance is confirmed. If any sample is positive, the participant will be retreated and followed up until clearance can be confirmed, to ensure no chronic carriage of SPA.

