### Sample size

The attack rate of the SPA challenge dose was estimated to be 58% on the comparator (Typhim Vi) arm, based on two previous CHIMs (22/38 participants).^43 48^ To show a VE of 70%, corresponding to an attack rate in the SII-TCV(B) arm of 17.4%, the study will need to recruit an effective sample size of 85 per arm. This is necessary to reject the null hypothesis that VE is ≤30% with 90% power at two-sided 0.05 significance level. Accounting for a dropout rate of 10% (although the attrition rate has been lower in enteric fever CHIMs), the final sample size needed is 192 volunteers.

This sample size will provide 90% power to demonstrate non-inferiority of SII-TCV(B) compared with Typhim Vi at a two-sided 0.05 significance level, assuming a 5% attrition rate. A few assumptions were used for the power calculation. First, to determine the non-inferiority of SII-TCV(B), we used WHO recommended non-inferiority margin of 0.67.^54^ Additionally, based on published data, SDs of anti-Vi IgG are 0.57 and 0.47 at log10 scale, respectively, in the Vi-PS and in the SII-TCV(B) arms, with a true geometric mean ratio (GMR) >1.2.^44^

For the primary paratyphoid endpoint (efficacy), the 30% superiority margin probably represents a stringent threshold for a VE trial using CHIM, as demonstrated in prior typhoid vaccine CHIM trials, in which VE was lower than observed in field trials,^44 55^ partly due to stringent predefined diagnostic criteria. Considering this, we conducted a sensitivity power calculation assuming the true VE is as low as 55% in the CHIM and concluded that the current sample size remains robust, providing 80% power to reject the null hypothesis that VE is ≤19% (see table 3).

**Table 3 T3:** Superiority margins at different study powers and associated vaccine efficacy

Vaccine efficacy	Superiority margin (90% power)	Superiority margin (80% power)
50%	8%	14%
55%	13%	19%
60%	19%	24%
65%	24%	30%
70%	30%	35%

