#### Chronic carriage

After treating and recovering from a typhoidal Salmonella infection, individuals may asymptomatically shed these bacilli in faeces. Up to 2%–5% of patients fail to clear the bacteria within 1 year, becoming chronic carriers and contributing to transmission.^64 65^ Over 90% of chronic carriers have underlying gallbladder disease, mainly calculi,^66^ thus only volunteers with a normal ultrasound examination of the gallbladder, performed at screening, will be eligible for inclusion.

The risk of chronic carriage is extremely low in the CHIM.^42 43 48 55^ The classes of the antibiotics used as first line in the trial are the preferred for carriage prevention.^67^,^69^ Participants will be required to bring stool samples after completing antibiotics to ensure clearance of faecal shedding of S. Paratyphi A.

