### AE reporting

Participants will self-record and grade (0–4) solicited symptoms in the electronic diary for 7 days after vaccination and for 21 days after challenge. Clinicians will regularly review diaries and may contact participants if clarifications are needed. Participants will also be able to record unsolicited symptoms for 28 days from vaccination and challenge, respectively. Solicited symptoms and severity grading of AEs are described in online supplemental tables S2–S6.

AEs related to vital signs recorded in clinic and clinically significant laboratory abnormalities will be reported from vaccination to day 180, whereas SAEs will be reported from consent signing until day 180 postchallenge. Additionally, AEs related to challenge for special consideration (AERC), listed in box 2, will be monitored from challenge day through day 180 postchallenge.

Solicited symptoms will be automatically presumed to be related to the vaccine or to the challenge, depending on the diary in which they were recorded. Clinicians will complete causality assessment for all other AEs, including unsolicited symptoms, throughout the study. Events will be considered related or not related to vaccination, challenge or other interventions (eg, antibiotics).

All SAEs and AERCs will be reported to the sponsor-delegated investigator and DSMC within 24 hours of notification. SAEs related to the vaccine will be reported as SUSAR within the required regulatory timelines.

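### Chronic carrier state is defined at one year or later after challenge, but Box 2 events are monitored only to day 180, so this one event cannot be met inside its stated window

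*Protocol article*

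**What the plan says.** Two statements in the protocol article set the terms for this event.

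- Box 2 (Safety and potential risks, Challenge) gives the definition: "Progression to chronic carrier state: defined as positive stool culture at least one year following challenge".
- The AE reporting section gives the observation period for AERCs: events "listed in box 2, will be monitored from challenge day through day 180 postchallenge". The legend of Figure 1 likewise gives days 90 and 180 as the last follow-up visits.

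Three other provisions bear on the point.

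- Under Follow-up visits, every participant brings three stool samples after antibiotics. If any is positive, "the participant will be retreated and followed up until clearance can be confirmed, to ensure no chronic carriage of SPA". No end date is attached.
- The item just before chronic carriage in Box 2 is convalescent shedding, defined by a positive stool one week or more after a second antibiotic course has finished.
- The reporting rule carries no day limit: "All SAEs and AERCs will be reported to the sponsor-delegated investigator and DSMC within 24 hours of notification".

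On background risk, the Chronic carriage section says that up to 2%–5% "of patients fail to clear the bacteria within 1 year, becoming chronic carriers and contributing to transmission". It then states: "The risk of chronic carriage is extremely low in the CHIM".

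**The concern.** A listed safety event should be able to occur within the period in which it is looked for. Here the definition starts at one year and the observation period stops at about six months. Whatever happens to participants, an AERC table built strictly on the stated window will show zero chronic carriers in both arms.

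What is at stake is how that zero is read. The article's list of strengths mentions "Rigorous screening procedures, including gallbladder ultrasound, prevention of chronic faecal carriage of" the challenge organism, and the Chronic carriage section describes the risk in this model as extremely low. A tabulated zero might be taken as fresh support for those statements, although the window allows no other result. The article does not plan such a use. Its statement of low risk rests on citations to earlier studies. The risk is one of presentation and of incomplete AERC recording. It is not a risk to the efficacy or immunogenicity conclusions.

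**Working it through.** The plan gives no figure of its own on this point, so there is none to reproduce. The check compares dates and then asks what the other rules already capture.

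**1. Definition against window.**
- Earliest qualifying culture: one year after challenge, taken as day 365 (Box 2).
- End of AERC monitoring: day 180 (AE reporting).
- Gap: 365 − 180 = 185 days. No culture taken by day 180 can satisfy the definition.

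**2. Is the problem shared by other Box 2 events?** No. Severe infection, failure of cure, convalescent shedding, relapse, transmission to a contact and medically attended events are all defined without requiring time beyond day 180. Only chronic carrier state is affected.

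**3. When would a persistent shedder be noticed?** Inputs:
- latest start of antibiotics for undiagnosed participants: day 14 (Antibiotics);
- first-line course: 4 + 10 = 14 days (Antibiotics);
- wait before the first stool: at least 7 days, with samples at least 48 hours apart (Follow-up visits).

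Calculation:
- First clearance stool: 14 + 14 + 7 = day 35.
- Third clearance stool: 35 + 2 + 2 = day 39.
- Assuming a second course, also of 14 days, starts at about day 39, the retest falls at 39 + 14 + 7 = day 60.

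These are the earliest dates the rules allow for someone treated from day 14. They ignore culture turnaround and late samples. Participants diagnosed sooner would reach each step sooner. A stool still positive at about day 60 meets the convalescent-shedding definition, 180 − 60 = 120 days before the window closes.

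**4. What a zero would appear to show.** The exact two-sided 95% upper limit for zero events in n participants is 1 − 0.025^(1/n).
- n = 192 (all randomised): 1 − 0.025^(1/192) = 0.0190, or 1.9%.
- n = 170 (2 × 85, from "the study will need to recruit an effective sample size of 85 per arm"): 1 − 0.025^(1/170) = 0.0215, or 2.1%.

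At face value these limits lie close to the low end of the 2%–5% quoted for patients. They do not apply to a zero that the window has fixed in advance. The comparison is also loose: the patient figure is a general one, whereas this trial requires a normal gallbladder ultrasound and treats everyone by day 14. The limits show only how such a zero could be misread.

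**The case against.** The strongest reply is that nothing of substance is lost. All participants are stool-tested after treatment, anyone positive stays under follow-up with no stated limit, and continued shedding after a second course is already a Box 2 event that would be recorded well inside the window. The 24-hour reporting rule has no cut-off, so a positive culture at one year in someone still under follow-up might well be reported in practice. The article also condenses a full protocol that is not shown.

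Most of this stands, and it limits the point. A reader might infer from the date mismatch that carriage follow-up stops at day 180, or that a zero count tells us nothing about carriage. The documents support neither reading. The clearance stools are informative: if every participant reaches three negative cultures, that is real, though indirect, evidence against carriage.

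What the reply does not remove is the contradiction. The article states both the definition and the window, and for this event both cannot apply as written. An open-ended reporting rule does not say that monitoring for this event extends beyond day 180. This is a conflict between two stated rules, not a detail left to a fuller document.

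**Conclusion.** The point holds as a narrow inconsistency. Chronic carrier state cannot be met within its stated monitoring period, which ends 185 days too early, so a zero count taken from that period is fixed by design and should not be presented as a finding. The evidence on carriage lies in the clearance stools and in the convalescent-shedding count.

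The size is small. The effect is confined to AERC recording for participants not cleared by day 180, possibly none. No primary or secondary outcome in Table 1 is affected, and no gap in participant care is shown.

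This conclusion takes the day-180 sentence literally for every Box 2 event and one year as 365 days. The view that carriage is otherwise well covered rests on complete stool sampling and on three negative cultures being good evidence of clearance. The article gives no culture sensitivity. A participant who clears on three samples and later sheds intermittently would not be detected at one year.

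**What to change.** In AE reporting, exempt chronic carrier state from the day-180 limit. A clause such as the following would do: for participants without confirmed faecal clearance, AERC monitoring continues beyond day 180 until clearance is confirmed or, failing that, to at least one year after challenge. In the safety tables, give the number of participants not cleared at day 180 beside the chronic-carriage count, so that readers can see how many were still at risk of the event as defined.

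The cost is one clause and longer recording for very few people, whom the Follow-up visits section already keeps under follow-up. For late challenges the recording could outlast the planned study end of September 2027. If the last day-180 visit fell at that end, the one-year point would come 185 days later. The clause adds no one-year stool for participants who have cleared, so it does not find later intermittent shedding. Routine one-year sampling of everyone is not proposed.

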### Antibiotics

Ciprofloxacin and azithromycin, which will be the first line of treatment, are generally well tolerated. However, ciprofloxacin has been associated with rare but potentially serious side effects, including neuropathy, arrhythmia, tendonitis, mood disturbances and aneurysms.^51 61 62^ These risks will be mitigated by reducing the exposure duration and by monitoring possible side effects via e-diary and phone call on day 21. Participants will be advised to contact the study team in case of any side effects.

Screening will exclude volunteers at increased risk of complications, including those with uncontrolled hypertension, depression or anxiety, prior intolerance to antibiotics that may be used in the trial, prolonged QT interval or family history of aneurysm. Counselling will address potential side effects of all antibiotics used, including provision of the MHRA leaflet on the use of ciprofloxacin.^63^ This will happen at screening, on challenge day and at the time of first dose of antimicrobial.

#### Chronic carriage

After treating and recovering from a typhoidal Salmonella infection, individuals may asymptomatically shed these bacilli in faeces. Up to 2%–5% of patients fail to clear the bacteria within 1 year, becoming chronic carriers and contributing to transmission.^64 65^ Over 90% of chronic carriers have underlying gallbladder disease, mainly calculi,^66^ thus only volunteers with a normal ultrasound examination of the gallbladder, performed at screening, will be eligible for inclusion.

The risk of chronic carriage is extremely low in the CHIM.^42 43 48 55^ The classes of the antibiotics used as first line in the trial are the preferred for carriage prevention.^67^,^69^ Participants will be required to bring stool samples after completing antibiotics to ensure clearance of faecal shedding of S. Paratyphi A.

#### Close contacts

Although unlikely, secondary transmission of the challenge strain to household or close contacts may occur via faecal-oral route. To minimise the risk, participants will be required to follow stringent handwashing practices and will receive detailed guidance on hygiene and preventing transmission. Soap and paper towels will be provided. Individuals in high-risk occupations (eg, food handlers and those working with vulnerable populations) will be excluded, unless they agree to abstain from work until clearance of infection is confirmed. Additionally, early treatment provided to participants will ensure rapid bacterial clearance, limiting the excretion period. These measures align with UKHSA guidance to safeguard public health.^70^

### AE reporting

Participants will self-record and grade (0–4) solicited symptoms in the electronic diary for 7 days after vaccination and for 21 days after challenge. Clinicians will regularly review diaries and may contact participants if clarifications are needed. Participants will also be able to record unsolicited symptoms for 28 days from vaccination and challenge, respectively. Solicited symptoms and severity grading of AEs are described in online supplemental tables S2–S6.

AEs related to vital signs recorded in clinic and clinically significant laboratory abnormalities will be reported from vaccination to day 180, whereas SAEs will be reported from consent signing until day 180 postchallenge. Additionally, AEs related to challenge for special consideration (AERC), listed in box 2, will be monitored from challenge day through day 180 postchallenge.

Solicited symptoms will be automatically presumed to be related to the vaccine or to the challenge, depending on the diary in which they were recorded. Clinicians will complete causality assessment for all other AEs, including unsolicited symptoms, throughout the study. Events will be considered related or not related to vaccination, challenge or other interventions (eg, antibiotics).

All SAEs and AERCs will be reported to the sponsor-delegated investigator and DSMC within 24 hours of notification. SAEs related to the vaccine will be reported as SUSAR within the required regulatory timelines.

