#### Challenge visit and challenge phase

At the challenge site, participants will be given a pre-treatment with sodium bicarbonate solution 1 min before being orally challenged with SPA (strain NVGH308) at the dose of 1–5×10^3^ CFU suspended in 30 mL of sodium bicarbonate on visit D0. Participants will fast for 90 min before and after challenge administration. They will be directly monitored for a minimum of 15 min, but they remain on site for 2 hours; if they vomit within 90 min of challenge administration, they will be withdrawn from the study and treated with antibiotics. During this observation, participants will be instructed and observed practising hand hygiene according to WHO’s guidance. They will be given access to an e-diary, where they will record solicited symptoms daily (as seen in online supplemental table S5) for 21 days, including twice-daily measured temperatures, and they may add any unsolicited symptoms and medications for 28 days.

Box 1 lists the prespecified criteria for diagnosis of paratyphoid infection: if presenting with at least one of them, participants will be considered susceptible to the disease, prompting antibiotic treatment. Recruited participants will be naïve to enteric fever, and baseline stool samples will be collected to ensure no SPA will be present prior to challenge. Since the UK is not endemic for enteric fever, and participants will not travel to endemic countries, we will assume that all SPA recovered from blood or stool culture will be the challenge strain.

Box 1Criteria for the diagnosis of paratyphoid A infectionParatyphoid A fever is diagnosed if any of the following applyA positive blood culture for SPA from 72 hours postchallenge.A positive blood culture for S. Paratyphi A within 72 hours postchallenge, with one or more signs/symptoms of paratyphoid A infection (such as recorded oral temperature ≥38.0^o^C).Persistent positive blood cultures (two or more blood cultures taken at least 4 hours apart) for S. Paratyphi A within 72 hours postchallenge.Oral temperature ≥38.0^o^C persisting for 12 hours or longer, not necessarily continuously.

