During the challenge phase, participants will be asked not to take any anti-pyretics to prevent interference with the diagnostic criteria. Participants will be seen daily until day 14, and if clinically indicated, an additional review will be arranged and symptomatic medications prescribed. Participants will be reviewed for 4 days after diagnosis, if applicable. At day 14, all undiagnosed participants will also take a full course of antibiotics.

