#### Antibiotics

Treatment will be given to all participants, either at the time of diagnosis or at day 14 postchallenge for those who did not reach preset criteria for diagnosis. Participants will be observed taking the first dose of antibiotic; subsequent doses of antibiotics will be taken by the participant at home, with compliance checked via e-diary. Other reasons for commencing antibiotics are listed in the online supplemental box S1.

A 14-day course of ciprofloxacin (500 mg two times per day) was the first-line antibiotic course used in previous paratyphoid fever CHIMs.^43 47 48^ However, due to potential risks associated with ciprofloxacin, highlighted by the Medicines and Healthcare products Regulatory Agency (MHRA) alert in 2024,^51^ alternative strategies to reduce exposure to this antibiotic were explored. According to the British Infection Association, both azithromycin and ciprofloxacin are recommended as optimal oral options to treat enteric fever.^52^ Evidence from enteric fever CHIMs indicates that ciprofloxacin outperforms azithromycin, with quicker clearance of fever and bacteraemia, as well as quicker symptom resolution,^53^ resulting in improved antibiotic tolerability and significantly fewer instances of antimicrobial switching (unpublished data). To leverage the rapid efficacy of ciprofloxacin while mitigating potential safety concerns and reducing exposure to it, a combination regimen of 4 days of ciprofloxacin (750 mg twice daily) followed by 10 days of azithromycin (1 g on the first day, 500 mg on following days) will be the first-line treatment in this trial.

Second-line or third-line courses of antimicrobials will be offered, should a participant develop intolerance to the first line. Online supplemental box S2 lists the alternatives. In case the participant requires intravenous antibiotics, ceftriaxone will be the choice.

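### Solicited symptoms in the 21-day challenge diary are all presumed challenge-related, although every participant starts antibiotics during that diary, so listed antibiotic reactions are merged with challenge reactions

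*Protocol article*

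**What the plan says.** The attribution rule is in the protocol article under AE reporting: "Solicited symptoms will be automatically presumed to be related to the vaccine or to the challenge", and the diary in which the symptom was entered decides which of the two applies. Individual assessment is kept for everything else: "Clinicians will complete causality assessment for all other AEs, including unsolicited symptoms, throughout the study". The sentence after that lists the possible causes as vaccination, challenge and other interventions, with antibiotics as the example.

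Under Challenge visit and challenge phase, participants receive an e-diary "where they will record solicited symptoms daily (as seen in online supplemental table S5) for 21 days". Unsolicited symptoms and medications can be added for 28 days. The same section states: "At day 14, all undiagnosed participants will also take a full course of antibiotics".

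The Antibiotics section under Trial Interventions states: "Treatment will be given to all participants, either at the time of diagnosis or at day 14 postchallenge". The first-line course there is 4 days of one drug followed by 10 of another. It differs from the regimen used in the earlier paratyphoid challenge studies. The first dose is taken under observation.

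The later Antibiotics section, on risks, says that ciprofloxacin risks will be reduced by a shorter exposure and by "monitoring possible side effects via e-diary and phone call on day 21".

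**The concern.** The rule gives a solicited symptom two possible causes, and the diary alone decides between them. For the challenge diary the answer is always challenge. Part of that diary is spent on antibiotics by every participant, including those never diagnosed. A listed symptom that first appears on day 16 in an undiagnosed participant, two days into treatment, is recorded as a challenge reaction, and no stated route allows another label.

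Two descriptive results are affected. Challenge reactogenicity takes in some antibiotic reactions, and antibiotic tolerability loses them. The second matters somewhat more than usual because the first-line regimen is new to this challenge model, and symptom profiles may be set beside those of the earlier studies.

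Applying one rule to both arms does not make its effect equal. Antibiotics start at diagnosis, and diagnosis is what the vaccine is meant to prevent, so antibiotic exposure inside the diary depends on arm if the vaccine works.

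**Working it through.** **Inputs from the article**
- Solicited challenge diary: 21 days from challenge (Challenge visit and challenge phase; AE reporting).
- Antibiotic start: at diagnosis, or at day 14 if undiagnosed (Antibiotics, under Trial Interventions).
- First-line course: 4 + 10 = 14 days (same section).
- Planned attack rates: 58% in the comparator arm, 17.4% with SII-TCV(B) (Sample size).
- Allocation 1:1, 192 in total, so 96 per arm (Randomisation; Sample size).

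**Assumptions.** The day of diagnosis, d, is not given, so a range is shown. Antibiotics are taken to start on day d, everyone is challenged, and everyone completes the first-line course.

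**The plan's own figure.** 22/38 = 57.9%, stated as 58%. With VE 70%, 0.58 × (1 − 0.70) = 0.174. The stated 17.4% is reproduced.

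**Antibiotic days inside the diary, per participant**
- Undiagnosed: 21 − 14 = 7 days (8 if both end days are counted).
- Diagnosed on day d: min(14, 21 − d) days, which is 14 for any d up to 7.

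**Mean antibiotic days per arm** = AR × (days if diagnosed) + (1 − AR) × 7. For d ≤ 7:
- Comparator: 0.58 × 14 + 0.42 × 7 = 11.06
- SII-TCV(B): 0.174 × 14 + 0.826 × 7 = 8.22

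| Day of diagnosis (assumed) | Days if diagnosed | Comparator | SII-TCV(B) | Difference |
|---|---|---|---|---|
| 7 or earlier | 14 | 11.1 | 8.2 | 2.8 |
| 9 | 12 | 9.9 | 7.9 | 2.0 |
| 11 | 10 | 8.7 | 7.5 | 1.2 |
| 13 | 8 | 7.6 | 7.2 | 0.4 |

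The difference equals (0.58 − 0.174) × (days if diagnosed − 7). It is zero when the attack rates are equal. Counting both end days, the first row's difference becomes 0.406 × (14 − 8) = 2.4.

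With VE 55%, the SII-TCV(B) attack rate is 0.58 × 0.45 = 26.1%. Diagnosis by day 7 then gives 11.1 v 8.8, a difference of 2.2.

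**People by treatment route**
- Diagnosed and treated on diagnosis: 96 × 0.58 ≈ 56 comparator, 96 × 0.174 ≈ 17 SII-TCV(B).
- Undiagnosed and treated at day 14: 96 × 0.42 ≈ 40 and 96 × 0.826 ≈ 79.
- Treated in total: 96 in each arm.

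**Endpoints.** Table 1 lists infection within 14 days, anti-Vi IgG at day 28 after vaccination, vaccine safety and immunogenicity. Its solicited events are limited to the 7 days after vaccination, before challenge and before any antibiotic.

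**The case against.** Several counter-arguments have force.

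**Antibiotic reactions are not lost altogether.** Unsolicited symptoms go through clinician assessment with antibiotics as a named cause, clinicians review the diaries, and there is a day 21 call. Only symptoms on the solicited list are caught by the rule. That list is not shown, so the overlap with antibiotic reactions cannot be judged. This limits the point without removing it.

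**The sentence listing possible causes might cover every event.** It follows directly on the sentence about all other AEs, and it does not displace an automatic presumption.

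**A uniform presumption has merit.** Real challenge illness can begin after treatment starts: the article expects most diagnoses to come from blood culture, with antibiotics within 24 hours. Case-by-case causality judgements would be made by clinicians who know diagnosis status, which differs by arm if the vaccine works. This stands, and it is why the fix does not ask for such judgements.

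A reader might also infer more than the article supports:
- **That the excess misattribution falls in the SII-TCV(B) arm**, because more of its participants start antibiotics undiagnosed at day 14. This leaves out the roughly 56 comparator and 17 SII-TCV(B) participants treated at diagnosis. Everyone is treated, so the same risk per person gives equal numbers in both arms, and counting days puts the excess in the comparator arm.
- **That everyone is on antibiotics through the end of the diary.** A 14-day course begun before day 7 ends before day 21.
- **That using the e-diary to watch for side effects contradicts the rule.** Monitoring and assigning cause are different tasks, so this is a tension only.

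**Conclusion.** The point holds in a limited form. Followed as written, the rule labels every solicited challenge-diary symptom as challenge-related while all participants spend part of that diary on antibiotics: about 7 days if undiagnosed and up to 14 if diagnosed by day 7, on the first-line course. A listed antibiotic reaction can only be counted as a challenge reaction.

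Under the planned attack rates the comparator arm has more antibiotic days in the diary, by about 0.4 to 2.8 days per participant over the range of diagnosis days shown. That imbalance requires a working vaccine, and its size rests on time to diagnosis, which is not given. The number of symptoms affected cannot be estimated, because neither the solicited list nor a rate of antibiotic reactions is available.

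The consequence is confined to descriptive reporting of challenge reactogenicity and antibiotic tolerability. A reader might infer that the safety comparison of the vaccines is compromised. It is not, since the solicited vaccine events in Table 1 end before challenge, and neither primary endpoint uses this attribution. The point is a worthwhile improvement and does not threaten the trial's conclusions.

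**What to change.** Keep the uniform presumption of relatedness to challenge for solicited symptoms with onset before the first antibiotic dose. Report solicited challenge-diary symptoms separately by onset before, and on or after, that dose, by arm and by diagnosis status. Describe those with onset on or after the dose as possibly related to challenge or to antibiotics, and not as challenge-related alone.

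This takes one sentence under AE reporting and one more split of the symptom tables. Diary entries are daily and the first dose is observed, so the dates needed should already be held. No treatment rule changes. The small downside is that symptoms arising after the first dose remain of mixed cause: the split shows the mixture without resolving it.
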